**Methods/Design:**

The study has two phases. We will conduct an initial descriptive study (Phase I) of supervision practices within public mental health in Washington State followed by a randomized controlled trial of gold standard supervision strategies (Phase II), with randomization at the clinician level (i.e., supervisors provide both conditions). Study participants will be 35 supervisors and 130 clinicians in community mental health centers. We will enroll one child per clinician in Phase I (N = 130) and three children per clinician in Phase II (N = 390). We use a multi-level mixed within- and between-subjects longitudinal design. Audio recordings of supervision and therapy sessions will be collected and coded throughout both phases. Child outcome data will be collected at the beginning of treatment and at three and six months into treatment.

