## Background

A substantial number of evidence-based treatments (EBTs) for child and adolescent mental health disorders exist, many with multiple randomized controlled trials (RCTs) supporting efficacy in improving outcomes and functioning [1]. EBTs are treatment approaches that have met strict criteria for efficacy based on rigorously controlled studies [2]. However, outcomes for youth served in community-based, public mental health settings have been less positive [3], and direct randomized comparisons of EBTs to usual treatment in such settings have shown variable findings and modest mean effect sizes [4,5]. Initial efforts to bridge the gap by providing access to EBTs through clinician training were mostly insufficient, as they did not include a focus on key implementation factors beyond training, and resulted in little to no change in clinician practice [6]. Therefore, EBT implementation in community-based settings has been viewed as proceeding at ‘an unacceptably slow pace’ [7]. Training in an EBT may be necessary—but not sufficient—to improve client outcomes for the average client served. Two recent reviews of clinician training concluded that training efforts must be active, multi-component, and attend to contextual factors such as organizational support [8,9]. One organizational support factor highlighted as critical, yet receives little research attention, is supervision. According to Herschell [9], the field requires ‘a better understanding of how supervisors should be trained and included in the implementation process.’ Clinical supervision and consultation are potentially the ‘least investigated’ aspects of implementation [10,11] despite findings that supervision accounts for a significant proportion of variance in client outcomes (16%) [12].

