### Phase II study

In Phase II of the study, all clinicians will be randomized to one of two supervision conditions: Symptom and Fidelity Monitoring (SFM) or SFM plus Behavioral Rehearsal (SFM + BR). We will randomize by clinicians because they are our primary unit of analysis. Supervisors will provide both conditions to balance the impact of individual supervisor/agency factors across conditions. We will monitor supervisor adherence to condition protocol and experimental drift through coding of audiotapes of supervision sessions. During Phase II, four randomly selected meetings per supervisor (two for each condition, distributed across participating clinicians) will be reviewed within a two-week window of the supervision meeting occurring (which is possible due to near real-time uploading with the use of the mobile device system) by research assistants blind to study condition. If experimental drift is identified, supervisors will be contacted within two weeks for a booster training on the supervision conditions. Supervisors will receive a biweekly email on condition adherence so that all supervisors receive regular communication from our team related to provision of supervision conditions.

Phase II has the added benefit of a within-subject design, in which clinicians retained from Phase I serve as their own controls prior to randomization. Given clinician attrition and replacement, some clinicians will not have Phase I data, and therefore will only be part of the between-subject analyses. Fidelity scores will be obtained from the three Phase II enrolled clients per clinician to obtain precise and reliable estimates of effect (see earlier ‘Objective TF-CBT fidelity’ section) and to increase statistical power for detecting differences between the two intervention conditions.

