### Aim 2: Evaluate effects of supervision condition (SFM vs. SFM + BR) on clinician fidelity and client outcomes (phase II)

#### Analyses

We will use Hierarchical Generalized Linear Models (HGLM) to test Aim 2, with the hypotheses that fidelity and client outcomes will be higher for SFM + BR than SFM and higher for SFM than supervision in Phase I. A two-level HGLM will predict fidelity using individual-mean fidelity scores for each client per clinician as the dependent variable and supervision as the independent variable for client functioning. These analyses are sufficiently powered at 0.8 to detect small effect sizes (0.35) with clinician-level Intraclass Correlations Coefficients (ICCs) less than 0.04 and small to moderate effect sizes (0.4) with ICCs as high as 0.21. To test for client functioning, we will build three-level longitudinal models, with level one variables representing time and child functioning scores, level two representing child-level factors, and level three representing clinician-related factors. These analyses are sufficiently powered at 0.8 to detect small effect sizes with clinician ICCs up to 0.24 and all conceivable moderate or large effects.

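### Supervisor is used as a balancing block in the Phase II design but has no term in either Aim 2 model, so the comparison of conditions is likely to be less precise than the design allows

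*Protocol article*

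**What the plan says.** The Phase II study section of the protocol article sets the unit of randomisation: "We will randomize by clinicians because they are our primary unit of analysis". It then gives the supervisor a design role: "Supervisors will provide both conditions to balance the impact of individual supervisor/agency factors across conditions". The abstract gives the numbers: "Study participants will be 35 supervisors and 130 clinicians in community mental health centers", with three children per clinician in Phase II (N = 390).

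The Aim 2 analyses are described by their levels. For fidelity: "A two-level HGLM will predict fidelity using individual-mean fidelity scores for each client per clinician as the dependent variable". For client functioning there are three levels: level one is time and the child's scores, with "level two representing child-level factors, and level three representing clinician-related factors". The power statements that follow use clinician-level ICCs only: 0.8 power for 0.35 with ICC below 0.04, for 0.4 with ICC up to 0.21, and, for client functioning, for a small effect with ICC up to 0.24. No supervisor or agency level, effect or ICC appears in the Aim 2 analyses.

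**The concern.** The design and the analysis treat the supervisor differently. About 130/35 = 3.7 clinicians share each supervisor, and the design removes supervisor differences from the comparison by having every supervisor run both arms. An analysis that stops at clinician does not know this. It counts supervisor variance as clinician variance and charges it to the contrast, although it has largely cancelled from the estimate.

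The article itself treats supervisors as a source of variation. Aim 1 reports supervisor-level means and variability, and Phase II monitors supervisors' adherence and retrains those who drift.

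At stake is the precision of the main randomised comparison: intervals wider than the design earns, and some lost power. There is also a smaller risk in the other direction. If some supervisors deliver BR more effectively than others, the condition effect itself varies by supervisor, and neither model allows for that.

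**Working it through.** **Inputs.** From the article: 35 supervisors, 130 clinicians, 3 children per clinician in Phase II, and clinician ICCs of 0.04, 0.21 and 0.24. Assumed: 1:1 allocation (65 clinicians per arm), two-sided alpha 0.05, total outcome variance 1, and a supervisor ICC between 0.02 and 0.16. The article states none of these.

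**The plan's own power figures.** Effective n per arm = 65 × 3 / (1 + 2 × ICC); SE = sqrt(2/n); power = Φ(d/SE − 1.96).

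- Fidelity, d = 0.35, ICC 0.04: n = 195/1.08 = 180.6, SE = 0.105, power 0.914.
- Fidelity, d = 0.4, ICC 0.21: n = 195/1.42 = 137.3, SE = 0.121, power 0.912.
- Client functioning, ICC 0.24, with small taken as 0.35: n = 195/1.48 = 131.8, SE = 0.123, power 0.811.

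The two fidelity statements do not reproduce at 0.80 with 130 clinicians. They do with about 93, so they are conservative, perhaps to allow for attrition, though the article does not say so. The client-functioning statement reproduces.

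**Effect of leaving supervisor out.** Let s, c and e be the supervisor, clinician and child variance shares, with s + c = 0.21 and e = 0.79. Per clinician mean, the model without supervisor uses s + c + e/3 = 0.21 + 0.263 = 0.473. With conditions balanced within supervisor, the contrast really carries only c + e/3 = 0.473 − s. The ratio of standard errors is sqrt(0.473 / (0.473 − s)):

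- s = 0.02: sqrt(0.473/0.453) = 1.02
- s = 0.05: sqrt(0.473/0.423) = 1.06
- s = 0.10: sqrt(0.473/0.373) = 1.13
- s = 0.16: sqrt(0.473/0.313) = 1.23

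A supervisor with three clinicians cannot be split evenly. The case was therefore also simulated with 25 supervisors of four clinicians and 10 of three, conditions balanced within supervisor, and 4,000 to 6,000 runs per case. Clinician means were analysed without supervisor and with supervisor as a fixed block.

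| Supervisor ICC | SE, omitted | SE, included | Type I error, omitted | Type I error, included |
|---|---|---|---|---|
| 0.02 | 0.120 | 0.119 | 0.048 | 0.050 |
| 0.05 | 0.121 | 0.116 | 0.036 | 0.048 |
| 0.10 | 0.120 | 0.108 | 0.031 | 0.051 |
| 0.16 | 0.120 | 0.099 | 0.021 | 0.055 |

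The excess width is therefore about 1% (simulated) to 2% (formula) at 0.02, 4-6% at 0.05, 11-13% at 0.10 and 21-23% at 0.16. At 0.16, power for d = 0.35 is 0.863 without supervisor and 0.932 with it. At 0.10, power for d = 0.4 is 0.933 against 0.951.

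**If the BR effect varies by supervisor.** Assume the supervisor-specific effect has variance 0.10 (SD = sqrt(0.10) = 0.32), with no supervisor main effect. This adds about 0.10/35 = 0.0029 to the true variance of the contrast, which the models do not fully see. Simulated type I error is about 0.07. A fixed block alone does not cure this (also about 0.07). With a supervisor ICC of 0.16 and the same interaction, type I error is 0.034 with supervisor omitted and 0.072 with the block but no interaction term.

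**The case against.** Several stronger readings are tempting. The article does not support them.

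- **That the 16% in the Background is the supervisor ICC.** It is a cited figure for how much of the variance in client outcomes supervision accounts for. The article does not call it between-supervisor variance, and it could not fit inside the fidelity scenario with ICC below 0.04. Here 0.16 serves only as the top of an assumed range; near 0.02 the effect is negligible.
- **That no planned model contains supervisor.** Aim 3 states no levels, and Aim 4 adjusts for covariates it does not name. Only Aim 2 fixes its levels. Clinician-related factors at level three could in principle include supervisor, but nothing says so, and the fidelity model's two levels leave no separate level for it.
- **That the randomisation may leave some supervisors with one condition only.** The abstract and the Phase II section both say supervisors provide both conditions, and the adherence review samples two meetings per condition for each supervisor. How the allocation list achieves this is detail for the full protocol.
- **That the stated power is wrong because of this.** At the article's total ICCs it is not. In the cases simulated, power falls below 0.8 only when a supervisor ICC of 0.16 is added on top of a clinician ICC of 0.21, for d = 0.35 (0.772 against 0.857 with supervisor included). The article makes no claim for that case.

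It is also fair to say that under balance the main error is conservative and does not raise the false-positive rate, and that drift monitoring limits differences in delivery between supervisors. Both points stand. They bear on the size of the problem and do not remove the mismatch in Aim 2.

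**Conclusion.** The point holds for Aim 2. The article makes supervisor a balancing factor and then specifies two models that stop at clinician. The consequence for SFM + BR versus SFM is lost precision: close to nothing at a supervisor ICC of 0.02, and about a fifth of the standard error at 0.16, where the nominal 5% test runs at about 2%.

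These sizes rest on an assumed supervisor ICC, a total clinician-level ICC of 0.21, 1:1 allocation and balance within supervisor. If clinicians were instead randomised without regard to supervisor, the standard error without a supervisor term would be about right (type I error 0.046-0.052). A reader should not infer a general false-positive risk: the anti-conservative case needs a condition effect that varies materially between supervisors. This is worth correcting because it is cheap, but it does not threaten the validity of the trial.

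**What to change.** Add supervisor, as recorded at randomisation, to both Aim 2 models, either as a random intercept or as a fixed block. The fidelity model becomes client, clinician, supervisor; the client-functioning model becomes time, child, clinician, supervisor. Carry the same term into the Aim 3 and Aim 4 models, and state the supervisor ICC assumed for power.

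Examine a supervisor-by-condition term as a sensitivity analysis. With 3.7 clinicians per supervisor there are about two per condition, so it will be weakly estimated. It should still be reported: a supervisor main effect alone removes the conservatism but does not protect against an effect that varies by supervisor.

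The cost is a change of analysis wording and one more variance term, or 34 degrees of freedom (35 − 1) for a fixed block. No new data are needed.

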### Aim 3: Test fidelity as a mediator of the relationship between supervision condition and client outcomes

#### Analyses

Mediational analyses will employ HGLMs using methods that extend traditional mediational modeling [77] to a multi-level longitudinal framework [78-80].

### Aim 4: Explore the relationship between supervision condition and broader implementation factors, including feasibility, acceptability, and impact on agency-relevant outcomes

#### Analyses

We will perform separate analyses on the dependent variables of turnover intention, actual turnover, burnout, supervision alliance, attitudes towards EBTs, and organizational climate. Mixed between- and within-subjects ANOVAs will test for differences between supervision conditions (between-clinician) and Phase I and Phase II (within-clinician) differences while controlling for important covariates. To examine feasibility and acceptability, we will use qualitative interview methods. Interviews will be transcribed and coded in the NVivo software program [81] using an integrated grounded theory approach to capture identified categories of interest as well as subcategories or emergent categories. Thematic content analysis, using the constant comparative method, also will be conducted [82,83].

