### Clinician and supervisor participants

Participants will include 35 supervisors and 130 clinicians from an estimated 15 to 20 agencies. Agencies were selected from those in the WA TF-CBT Initiative with consideration of statewide geographic representation. Each agency has one to four supervisors and a potential clinician participant pool of 2 to 15 qualifying clinicians based on study inclusion and exclusion criteria. Eligible supervisors were identified during study development with additional supervisors recruited at the beginning of Phase I. Eligible clinicians must be: trained in TF-CBT as part of the WA TF-CBT Initiative and/or have completed the TF-CBT web training with at least one TF-CBT case underway; at least 50% FTE employees at one of the participating agencies; supervised by one of the participating supervisors; and able to provide TF-CBT in English. We propose only two exclusionary criteria: immediate plans to leave the agency or transition into a non-child/adolescent caseload carrying position. Clinicians and supervisors who exit the study will be replaced with new clinicians and/or supervisors who are similarly trained in TF-CBT and study protocols.

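### The Aim 4 mixed ANOVA cannot include randomised replacement clinicians who lack a Phase I score, and the condition term it names averages in pre-randomisation scores, which halves a Phase II effect

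*Protocol article*

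**What the plan says.** The analysis paragraph under Aim 4 lists six dependent variables: "turnover intention, actual turnover, burnout, supervision alliance, attitudes towards EBTs, and organizational climate". It names one quantitative method for them: "Mixed between- and within-subjects ANOVAs will test for differences between supervision conditions (between-clinician) and Phase I and Phase II (within-clinician) differences". The sentence adds adjustment for covariates, which it does not name. It mentions no condition-by-phase interaction and no separate comparison restricted to Phase II.

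The Phase II study section states that "all clinicians will be randomized to one of two supervision conditions", and that "clinicians retained from Phase I serve as their own controls prior to randomization". Phase I scores therefore precede randomisation. The same section says: "Given clinician attrition and replacement, some clinicians will not have Phase I data, and therefore will only be part of the between-subject analyses". The section on clinician and supervisor participants explains where these clinicians come from: "Clinicians and supervisors who exit the study will be replaced with new clinicians and/or supervisors".

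This point concerns the five outcomes that can be scored in both phases. Actual turnover is an event rather than a repeated score and is left aside.

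**The concern.** There are two difficulties, and both lie in the method as stated.

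**Who is analysed.** Randomised clinicians without a Phase I score are expected by design. In its standard form, a mixed between/within ANOVA needs a score from each clinician at each level of the within factor. A replacement therefore drops out of the whole fit, including the condition test, although the Phase II study section keeps that clinician for between-subject comparisons. The one method named for Aim 4 cannot carry out that rule.

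**What is compared.** The Aim 4 sentence ties the condition comparison to the between-clinician factor. In a two-phase mixed ANOVA, that term compares the conditions on each clinician's average over both phases. Randomisation makes the expected Phase I difference zero, so the average contains only half of any effect that arises in Phase II.

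At stake is the randomised SFM versus SFM + BR comparison on the outcomes that matter to agencies. A real difference could be missed, or reported at half its size, because the pre-randomisation data are used in a way that weakens the test.

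**Working it through.** The article gives no power, effect size or attrition figure for Aim 4, so there is no stated figure to reproduce. The calculation below compares possible tests under assumptions.

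**Inputs from the article:** 130 clinicians; Phase I before randomisation; some randomised clinicians without Phase I data (number not given).

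**Assumptions:** 1:1 allocation, so 130/2 = 65 per condition; SD 1 in each phase; true Phase II difference d = 0.5 SD; correlation ρ between phases of 0.3, 0.5 or 0.7; two-sided 5% test; 30% of clinicians lacking a Phase I score but having a Phase II score, so 65 × 0.7 = 45.5 complete per condition. Clustering by supervisor is ignored.

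**Formula.** For n clinicians per condition and variance factor v, SE = √(2v/n) and power = Φ(effect/SE − 1.96).

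- Between-clinician term: effect (0 + d)/2 = d/2, v = (1 + ρ)/2.
- Condition-by-phase interaction (difference in change): effect d, v = 2(1 − ρ).
- Phase II scores only: effect d, v = 1.
- Phase II scores adjusted for Phase I: effect d, v = 1 − ρ².

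**Numbers at ρ = 0.5.**

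- Between-clinician, complete data: effect 0.25; SE = √(1.5/65) = 0.152; 0.25/0.152 = 1.65; power Φ(−0.31) = 0.38.
- Between-clinician, 30% lacking a phase: SE = √(1.5/45.5) = 0.182; 0.25/0.182 = 1.38; power Φ(−0.58) = 0.28.
- Phase II only, all 65 per condition: SE = √(2/65) = 0.175; 0.5/0.175 = 2.85; power Φ(0.89) = 0.81.

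**Across correlations.**

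| ρ | Between term, complete | Between term, 30% lost | Interaction, complete | Interaction, 30% lost | Phase II only, all randomised |
|---|---|---|---|---|---|
| 0.3 | 0.424 | 0.315 | 0.673 | 0.522 | 0.813 |
| 0.5 | 0.377 | 0.280 | 0.813 | 0.665 | 0.813 |
| 0.7 | 0.339 | 0.253 | 0.957 | 0.868 | 0.813 |

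At ρ = 0.5, varying the loss from 10% to 40% moves the power of the between-clinician term from 0.345 to 0.247.

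A simulation of 20,000 trials at ρ = 0.5 agrees. The mean between-clinician estimate was 0.250 for a true d of 0.5. Its power was 0.371 with complete data and 0.273 with 46 complete clinicians per condition.

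Adjusting Phase II scores for Phase I would give 0.85, 0.91 and 0.98 at the three correlations if everyone had a Phase I score. This is an upper bound, because replacements have none.

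**The case against.** The strongest reply is that the Phase II study section already settles the matter. Replacements belong in between-subject comparisons only, and the Aim 4 sentence is a one-line summary, in the plural, to be read in that light. Nowhere does the article say that incomplete clinicians are deleted, and a condensed article may leave such handling to a fuller document. This shows what the authors intend. It does not supply a method that does it: the method named, in its usual form, does not accept a clinician with one score.

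A second reply is that any mixed ANOVA also yields the condition-by-phase interaction, and that the unnamed covariates might include the Phase I score. The interaction is indeed not diluted, and at a high correlation it does well even with clinicians lost (0.868 at ρ = 0.7). But the article does not name it, it still omits the replacements, and at ρ = 0.5 its power falls from 0.813 to 0.665 with 30% lost. A reader should not infer that every test from this ANOVA is halved; only the between-clinician term is.

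A reader might also infer that the ANOVA biases the result by dropping leavers. The article does not support that. Clinicians who exit before Phase II are never randomised, so losing them does not bias the randomised contrast. Those who exit later without a Phase II score lack it under most methods. No section says that leavers have the highest burnout, and no rate of leaving, overall or by condition, is given.

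Finally, Aim 4 is exploratory and carries no power claim. That stands, and it limits the severity.

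**Conclusion.** The point holds for the five survey outcomes. The stated method cannot include the replacements whom the article keeps for between-subject comparisons, and the condition term it names estimates d/2 rather than d. Both follow from the text and the structure of a standard mixed ANOVA, without numerical assumptions.

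The size does depend on assumptions. With d = 0.5 SD, 65 per condition and ρ = 0.5, power for the named term is about 0.38 with complete data and 0.28 with 30% lacking a phase, against 0.81 for simply comparing Phase II scores in all randomised clinicians. The effect size, correlation and share of clinicians lost are not in the article, so these figures are an illustration and not a forecast.

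The severity is modest. Aim 4 is exploratory, and the fidelity and client-outcome analyses of Aims 2 and 3 use other models and are untouched. The conclusion is lost information and a diluted contrast; it does not extend to bias from leavers.

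**What to change.** For turnover intention, burnout, supervision alliance, attitudes to EBTs and organisational climate, replace the mixed ANOVA with a likelihood-based linear mixed model that uses every available score from all randomised clinicians, including replacements with a Phase II score only. Define the SFM versus SFM + BR test as the condition difference at Phase II, with Phase I means constrained to be equal across conditions, as randomisation implies. Report the Phase I to Phase II contrast separately, since it is not a randomised comparison.

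Under the illustration at ρ = 0.5, power would lie between the Phase II-only value of 0.81 and the fully adjusted bound of 0.91, depending on how many clinicians have a Phase I score.

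The cost is a change of wording and slightly more modelling work. The team already plans hierarchical models for Aims 2 and 3, and no extra participants or data collection are needed.

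### Aim 4 tests actual turnover within clinicians across phases, but only those who stayed through Phase I can contribute, so the contrast can show only no change or a rise

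*Protocol article*

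**What the plan says.** The Analyses paragraph under Aim 4 announces separate analyses of the "dependent variables of turnover intention, actual turnover, burnout" and three further variables: supervision alliance, attitudes towards EBTs and organizational climate. Actual turnover is therefore an outcome in its own right, distinct from turnover intention. The next sentence gives the method: "Mixed between- and within-subjects ANOVAs will test for differences between supervision conditions (between-clinician) and Phase I and Phase II (within-clinician) differences", with covariate adjustment. No variable is excepted, and no other quantitative method is given for turnover.

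Three statements elsewhere in the article decide who can enter the within-clinician part:

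- Phase II study: "clinicians retained from Phase I serve as their own controls prior to randomization".
- Phase II study, on those who join later: "some clinicians will not have Phase I data, and therefore will only be part of the between-subject analyses".
- Clinician and supervisor participants: "Clinicians and supervisors who exit the study will be replaced with new clinicians and/or supervisors". The same section requires clinicians to be "at least 50% FTE employees at one of the participating agencies", so a clinician who leaves that employment is no longer eligible.

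**The concern.** A within-clinician phase contrast needs a value from the same person in each phase. Leaving is an event that normally ends a person's participation. A clinician who leaves in Phase I has no Phase II value, and the replacement has no Phase I value. The clinicians who remain for the contrast are those who did not leave in Phase I, so their Phase I outcome is fixed before any data are seen.

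At stake is the direction of a result that agencies would care about. The Background cites evidence linking EBT coaching in supervision with less actual turnover among clinicians, and the Aim 4 heading names agency-relevant outcomes. The planned phase contrast could never show a reduction, however well either supervision condition worked, and would usually show an increase even if nothing had changed.

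**Working it through.** The article gives no turnover rate, power or error rate for Aim 4, so there is no stated figure to reproduce. The check is a structural argument followed by a calculation of its size.

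**Structure.** Code turnover as 1 if the clinician leaves in a phase and 0 otherwise.

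| Clinician | Phase I | Phase II | In the within-clinician contrast? |
|---|---|---|---|
| Leaves in Phase I | 1 | none | no |
| Replacement, joins later | none | 0 or 1 | no |
| Stays through both phases | 0 | 0 | yes |
| Stays through Phase I, leaves in Phase II | 0 | 1 | yes |

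Only 0→0 and 0→1 enter. The mean within-clinician difference is therefore (leavers in Phase II) ÷ (clinicians with both phases), which cannot be negative. The Phase I values have no variance.

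**Inputs for the size.**
- 130 clinicians (Clinician and supervisor participants).
- The same true turnover probability p in each phase and no condition effect, so that any phase difference found is false.
- p from 5% to 40% per phase: an assumption.
- Two-sided 0.05, also an assumption; 4,000 simulated trials per value of p.

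**Clinicians expected in both phases:** 130 × (1 − p). For p = 5% this is 130 × 0.95 = 123.5; for p = 20% it is 130 × 0.80 = 104; for p = 40% it is 130 × 0.60 = 78.

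**Simulated 2 × 2 mixed ANOVA:**

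| p per phase | Mean number in both phases | Phase I turnover analysed | Phase II turnover analysed | Phase effect significant | Condition-by-phase significant |
|---|---|---|---|---|---|
| 5% | 123.4 | 0 | 5.0% | 87.3% | 4.8% |
| 10% | 117.0 | 0 | 10.0% | 99.8% | 5.5% |
| 20% | 104.0 | 0 | 19.9% | 100% | 5.2% |
| 30% | 91.0 | 0 | 29.9% | 100% | 5.0% |
| 40% | 77.9 | 0 | 40.0% | 100% | 4.9% |

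Every significant phase effect in this table is a false increase.

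**Hand check at p = 5%.** With n = 123 clinicians in both phases and k Phase II leavers, the mean difference is k/n, its standard error is √[(k/n)(1 − k/n)/(n − 1)], and t is their ratio.
- k = 3: 0.0244 ÷ 0.01397 = 1.75, p-value about 0.08.
- k = 4: 0.0325 ÷ 0.01606 = 2.02, p-value about 0.045.

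Four leavers are enough for significance. With an expected 123 × 0.05 = 6.15 leavers, the binomial probability of four or more is 0.868, in line with the simulated 87%.

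**What survives.** Because Phase I is constant at 0, the condition-by-phase test is simply the between-condition comparison of Phase II turnover. Its error rate in the last column stays near 5%.

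**The case against.** The strongest case on the other side has five parts.

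*The aim is exploratory.* Its heading says so, turnover is one of six variables, and the heading's target is the effect of supervision condition, which is the randomised comparison. Aims 2 and 3 are untouched. This stands and limits the weight of the point.

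*A condensed article may leave the detail to a fuller document.* One sentence covers six variables of different types, and the exact model for a yes/no outcome or for unequal time at risk could well be specified elsewhere. That answers a complaint about ANOVA on a binary outcome, which is not pressed here. It does not answer this point: the article states the contrast and applies it to turnover without exception.

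*Zero is not absolute.* Actual turnover is not defined in the article. A clinician who moved from one participating agency to another in Phase I might count as turnover and still be eligible. The article describes no such route. A few such cases would not repair the contrast, but strictly zero is too strong, hence the qualification.

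*Turnover might be counted as an agency or supervisor rate.* The sentence says within-clinician, so the text does not support that reading.

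*The investigators already urge caution.* The Limitations section says that Phase I versus Phase II conclusions may be limited. The reason given is that child cases could not be randomised between phases; selection on staying in post is a different problem.

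A reader might also infer that the burnout, turnover-intention, alliance, attitude and climate results would come from stayers only. The documents do not support that. Those are repeatable measures, nothing prescribes a complete-pair analysis, and clinicians without Phase I data are expressly kept in the between-subject analyses.

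**Conclusion.** The point holds for one contrast. As written, the Phase I versus Phase II within-clinician test of actual turnover has its direction set by selection. With equal true turnover in both phases it would falsely show a rise in about 87% of trials at 5% per phase, 99.8% at 10%, and essentially all at 20% to 40%. These figures rest on the assumed rates, on clinicians leaving independently of one another, and on no moves between participating agencies being counted as turnover. The sign restriction does not depend on the assumed rate.

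Two stronger conclusions are tempting. One is that the turnover analysis as a whole is invalid: it is not, because SFM versus SFM + BR can be compared on Phase II turnover and that test keeps its error rate. The other is that the trial would report harm from the new supervision: that presumes nobody would notice that retained clinicians had, by definition, not left. The article supports saying that the contrast misleads if followed, and no more. It deserves correction, but it does not threaten the trial's main aims.

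**What to change.** - State that actual turnover is excluded from the within-clinician phase contrast.
- Compare it between SFM and SFM + BR in Phase II, among all randomised clinicians, with a binary model. A time-to-event model from randomisation is an option if dates of leaving the agency are recorded; the article mentions replacement of those who exit the study but does not say that such dates are kept.
- Allow for supervisor clustering with a random effect. With 130 ÷ 35 = 3.7 clinicians per supervisor on average, stratifying a Cox model by supervisor would lose every stratum without an exit.
- Define actual turnover, including whether a move between participating agencies counts.
- Give any phase comparison descriptively only, as exits among all clinicians at risk in each phase, leavers and replacements included.

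The analyses of the repeatable scales need no change on this account. The cost is analysis wording and a definition; design and sample size stay as they are, and no new data are needed for the binary comparison beyond knowing who left.
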